### Interventions

A clinician is responsible for assessing the patient’s condition on the ward, determining whether the patient meets the inclusion criteria, and informing the patient of the purpose of the trial, methods, possible risks, and rights of participants. Patients who meet the inclusion criteria will sign an informed consent form after agreeing to participate in the trial. The project manager will group patients who agree to participate in the trial based on the randomly assigned list and escort the patient to the treatment room, where the trial will be conducted. All patients in the trial will receive routine treatment (oral pregabalin 75 mg twice daily). Patients in the intervention group will inhale nitrous oxide/oxygen mixture with a facemask, which is a visible intervention measure. To eliminate the influence of psychological factors on the experimental results of patients in the control group, patients in the control group will inhale oxygen by a facemask. Patients in the intervention group will receive routine treatment plus a fixed nitrous oxide/oxygen mixture (contains 65% nitrous oxide and 35% oxygen), while patients in the control group will receive routine treatment plus oxygen. Before inhaling the gas, the data collector will teach the patient to use the NRS to report pain intensity. Besides, the data collector will inform patients that they have the right to stop or quit the trial at any time if they experience discomfort during the study. Before the trial begins (T0), the data collector will record the patient’s demographic and baseline characteristics; assess the patient’s pain intensity; measure heart rate, blood pressure, and percutaneous oxygen saturation; and teach the patient to inhale gas using a facemask. Patients in both groups will inhale gas using an oral-nasal mask, which is disposable and has a one-way valve. According to our previous research, the gas intake will last for 15 min [33, 34]. When the data collector opens the valve of the cylinder and the patient puts on the mask to inhale the gas, the trial will start timing. The data collector will assess the patient’s pain intensity and measure blood pressure, heart rate, and percutaneous oxygen saturation at the beginning of the trial at 5 min (T1) and 15 min (T2). To assess the patient’s pain, the data collector will ask the patient: How bad is the pain now? Patients will point to the corresponding pain score with their fingers and without having to remove the facemask. Five minutes after the end of the trial (T3), in addition to collecting the data mentioned above, the data collector will ask patients about their satisfaction with pain relief and acceptance of analgesic methods. Throughout the trial, the data collector will closely observe and ask the patient whether there are adverse effects.

Nitrous oxide/oxygen mixture has been widely used for pain relief with mild adverse effects and quick recovery [29]. Adverse effects of nitrous oxide/oxygen mixture have been reported in the literature, including nausea, vomiting, dizziness, drowsiness, headache, hypotension, and oxygen desaturation [29]. These adverse reactions usually do not require medication and recover quickly [29]. If any adverse effects occur or the patient requests that the trial be discontinued, the data collector can determine whether the trial should continue. The reason for trial stopped will be recorded by the data collector. The project manager will accompany the patient to participate in the trial but does not involve in the collection of trial data. Only the project manager knows what kind of gas the patient is breathing. During the trial, the project manager will take treatment measures if the patient has adverse effects.

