### Participant retention and withdrawal

To improve patients’ ability to adhere to the intervention, researchers will do the following strategies. First, the investigator will explain to the patient in detail the purpose of the study, the methodology, the possible risks, and the rights of the participants. Second, the researchers will closely monitor patients’ physiological parameters during the trial to ensure the safety of their lives. If patients have any discomfort during the trial, they will be available for medical treatment at any time. Third, patients who complete the trial will receive a free visit from a pain specialist. The investigator will create a chart to record the patient’s adherence to the trial. Patients can ask to withdraw from the trial at any time without affecting subsequent treatment. The data collector will record and analyze the reasons for the withdrawal.

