### Data collection, management, and confidentiality

Members of the research team will be trained before the study. The training includes protocols for trial design (e.g., how to achieve double blindness), use of gas devices (e.g., use of facemask), data collection (e.g., how to assess a patient’s pain intensity), and experimental contingency planning (e.g., management of adverse effects in patients). Besides, data collectors and investigators will be fixed during the trial, and data will be double-entered to ensure accuracy. The Data Monitoring Committee (DMC) members will periodically review the database to improve data quality (see the “Data monitoring” section).

Patients will participate anonymously and their personal information will not be disclosed. The patient’s anonymous code will be randomly generated by the computer and kept by the project manager. The trial data will be stored in a folder on the computer that can only be accessed through password authentication. Researchers can check this data only with the authorization of the project manager. When the experiment is complete, the researchers will have access to the data for statistical analysis.

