Starting with gas inhalation, the data collectors will carefully observe and record any adverse effects on the patient. The expected adverse effects of nitrous oxide/oxygen mixture therapy include nausea, vomiting, dizziness, drowsiness, headache, hypotension, and oxygen desaturation [29]. If any adverse effects occur, the study will be terminated immediately, the patient will be given oxygen, and the adverse effects will be fully reversible in 5 min [43]. Any adverse effects concerning the intervention will be recorded throughout the trial period.

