### Data monitoring

The DMC will be set up at the same time the research project is identified. The DMC includes a pain management specialist, a chief pharmacist, a chief nurse, and a statistical specialist who chairs the DMC. During the implementation of the study, members of the DMC will review the original test data every month, check the standardization of the study, ensure the completeness and accuracy of the data, and guarantee the credibility and dependability of the study results. If the study is not performed as planned, the DMC will make corrective recommendations or stop the study. Any deviations from the trial will be recorded in the breach report form, and the study team will discuss and propose a modification plan. Update clinical trial registration information as necessary.

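### The Interventions section lets the data collector decide whether a session continues after an adverse effect or a patient's request to stop, at odds with the stopping and withdrawal rules elsewhere in the protocol

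*Protocol article*

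**What the plan says.** Four places in the protocol article bear on when a session stops.

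- **Interventions, on adverse effects and requests to stop:** "If any adverse effects occur or the patient requests that the trial be discontinued, the data collector can determine whether the trial should continue". The next sentence adds: "The reason for trial stopped will be recorded by the data collector".
- **Measurement, on adverse effects:** "If any adverse effects occur, the study will be terminated immediately, the patient will be given oxygen". Just before this, the section says: "The expected adverse effects of nitrous oxide/oxygen mixture therapy include nausea, vomiting, dizziness, drowsiness, headache", and it goes on to name low blood pressure and falling oxygen saturation.
- **Interventions, on what patients are told before inhalation:** "they have the right to stop or quit the trial at any time if they experience discomfort during the study".
- **Participant retention and withdrawal:** "Patients can ask to withdraw from the trial at any time without affecting subsequent treatment".

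No section reconciles these statements, for example by grading severity or by separating an end to the gas from leaving the study.

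**The concern.** A safety rule should tell the person at the bedside one thing. Here the same event, any adverse effect, leads to discretion in one section and to a mandatory stop with oxygen in another. The events in question are ones the protocol expects, such as dizziness or drowsiness, so the choice between the rules could well arise.

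The second trigger matters more in principle. A request to stop should end inhalation without anyone else's agreement. The Interventions sentence puts that request beside adverse effects and leaves both to the data collector. What is at stake is participant protection and consistent conduct of the sessions.

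**Working it through.** No figure in the plan depends on this point, so the check is a comparison of texts.

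**Step 1: do the sentences concern the same thing?** The Interventions sentence speaks of the trial and the Measurement sentence of the study. Both make sense only as the individual patient's 15-minute session. Interventions starts timing the trial when the mask goes on, and Measurement gives oxygen to the patient concerned.

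**Step 2: is the trigger the same?** Yes. Both sentences open with the occurrence of any adverse effect, and both sections list the same seven expected effects. Neither limits its rule to serious or unexpected events.

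**Step 3: compare the actions.**

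| Event | Interventions sentence | Other sections |
|---|---|---|
| Any adverse effect | Data collector decides whether to go on | Measurement: stop at once and give oxygen |
| Patient asks to stop | Data collector decides whether to go on | Interventions: right to stop on discomfort. Participant retention and withdrawal: may ask to leave at any time |

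**Step 4: when do the rules collide?** Take a patient who becomes dizzy at minute 6.

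- If the data collector stops the gas and gives oxygen, both sections are satisfied, because the Interventions sentence permits continuation but does not require it.
- If the data collector lets the session run on, the Interventions sentence is satisfied and the Measurement rule is broken.

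The conflict therefore exists only where the discretion is used to continue.

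**Step 5: the patient's request.** The right described in Interventions is tied to discomfort, and the withdrawal section says that patients can ask, which is softer than naming a right. Even so, neither makes stopping depend on staff agreement. A patient who asks to stop because of discomfort falls squarely under the stated right, so the sentence that makes it a data-collector decision is the one out of line.

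**The case against.** The strongest reply is that this is loose drafting. The sentence that follows concerns the recording of why a session stopped, which suggests that the authors meant to give the data collector authority to end a session. The same data collector tells each patient beforehand of the right to stop. There are other safeguards too: the project manager stays with the patient and treats adverse effects, and the withdrawal section promises medical treatment whenever there is discomfort. This reply largely stands and is why the point is minor. It does not remove the point, because the sentence as written covers a decision that the session goes on.

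A second reply is that discretion could be the intended rule, since the Interventions section describes the known adverse effects as mild and quick to resolve. That is possible, but then the Measurement rule would have to change. The two cannot both stand unqualified.

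Some stronger readings are tempting and are not supported:

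- **That staff cannot comply with both rules.** They can, by always stopping.
- **That a patient's request may be refused.** No section says so; the wording only leaves room for it.
- **That training and deviation reporting lack a single rule.** The article names a training topic, "experimental contingency planning (e.g., management of adverse effects in patients", and says "Any deviations from the trial will be recorded in the breach report form", but shows the content of neither. Either could settle the matter.
- **That the number of participants still to be recruited measures the problem.** Trial status gives 20 recruited of the 42 planned, which leaves 42 − 20 = 22. That count says nothing about how often the conflict arises.

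**Conclusion.** The inconsistency is real and minor. The Interventions sentence permits continuation after an adverse effect where the Measurement section requires an immediate stop with oxygen. It also puts a patient's request to stop under a staff decision, despite the right to stop and the option to withdraw given elsewhere. This is a conflict between rules that the article states, so condensation from a fuller protocol does not explain it.

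No numerical effect is claimed. A reader might infer bias between the arms, since adverse effects may be more frequent with nitrous oxide and the stopping rule decides who is still inhaling at 5 and 15 minutes. The article gives no adverse-effect rates by arm and no information on how often sessions were continued or cut short, so that inference cannot be supported or sized.

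The conclusion rests on one assumption: that trial and study in the two sentences mean the individual session.

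**What to change.** Replace the Interventions sentence with wording such as:

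> If the patient asks to stop, inhalation ends at once. If an adverse effect occurs, inhalation ends immediately and the patient is given oxygen, as stated under Measurement. The data collector may also end a session at any time for safety.

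The first part gives effect to the patient's right to stop. The second adopts a rule that the protocol already contains. The third keeps the probable intent of the present sentence.

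Add that, after an early stop, the remaining scheduled NRS and physiological assessments are still collected where the patient agrees. This suits the intention-to-treat analysis named under Statistical analysis and limits missing values. Keep recording the reason for each stop, as already planned, and record the date of the clarification, because recruitment had begun and earlier sessions may have been run under the discretionary wording.

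The cost is a short text change, with no extra patients, visits or data items. The downside is that some sessions may end before the 15-minute assessment, including for mild effects. The Measurement section already implies this, so it is not a new burden.

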### Participant retention and withdrawal

To improve patients’ ability to adhere to the intervention, researchers will do the following strategies. First, the investigator will explain to the patient in detail the purpose of the study, the methodology, the possible risks, and the rights of the participants. Second, the researchers will closely monitor patients’ physiological parameters during the trial to ensure the safety of their lives. If patients have any discomfort during the trial, they will be available for medical treatment at any time. Third, patients who complete the trial will receive a free visit from a pain specialist. The investigator will create a chart to record the patient’s adherence to the trial. Patients can ask to withdraw from the trial at any time without affecting subsequent treatment. The data collector will record and analyze the reasons for the withdrawal.

### Data collection, management, and confidentiality

Members of the research team will be trained before the study. The training includes protocols for trial design (e.g., how to achieve double blindness), use of gas devices (e.g., use of facemask), data collection (e.g., how to assess a patient’s pain intensity), and experimental contingency planning (e.g., management of adverse effects in patients). Besides, data collectors and investigators will be fixed during the trial, and data will be double-entered to ensure accuracy. The Data Monitoring Committee (DMC) members will periodically review the database to improve data quality (see the “Data monitoring” section).

Patients will participate anonymously and their personal information will not be disclosed. The patient’s anonymous code will be randomly generated by the computer and kept by the project manager. The trial data will be stored in a folder on the computer that can only be accessed through password authentication. Researchers can check this data only with the authorization of the project manager. When the experiment is complete, the researchers will have access to the data for statistical analysis.

### Measurement

We will use a form to collect the baseline characteristics of patients, including age, gender, weight, height, education level, employment status, medical burden (no burden at all, basically no burden, some burden, heavy burden), location of pain, and course of the disease. Besides, the patients’ pain intensity, physiological parameters (blood pressure, heart rate, percutaneous oxygen saturation), patients’ acceptance of the analgesia, patients’ satisfaction with pain relief, and adverse effects will be recorded.

NRS will be used to assess the intensity of pain, ranging from 0 to 10, where 0 means “painless” and 10 means “worst pain imaginable” [38]. In most cases, clinicians and patients tend to use NRS to assess pain levels. Patients choose a number to represent their pain degree according to their feelings, which is easy to be understood by patients, is easy to use, and even can obtain scores in oral use, with high reliability and validity [39]. The reliability of the NRS has been proven to be moderate to high, with a maximum of 0.96. Besides, the convergence validity of NRS is 0.79 to 0.95 [40]. The patients’ physiological parameters will be monitored with an electronic sphygmomanometer (OMRON, HEM-7120) and oximeter (PC-60B). Pain intensity and the physiological parameters will be monitored simultaneously at baseline (T0), 5 min (T1), and 15 min (T2) after the trial began and at 5 min (T3) after the trial ended. Patients’ satisfaction with pain relief will be measured by a 5-point Likert scale (5, very satisfied; 4, satisfied; 3, uncertain; 2, dissatisfied; 1, very dissatisfied) [41]. The 5-point Likert scale is one of the Likert scales. Likert scale plays an important role in psychological research, which is the main method to measure attitude and personality. Besides, the Likert scale is easy to implement [42]. Furthermore, the data collectors will inquire into the patient’s acceptance of analgesia by asking the patient whether they would accept the gas inhalation to ease the pain (yes/no). Satisfaction and acceptance will be investigated at T3.

Starting with gas inhalation, the data collectors will carefully observe and record any adverse effects on the patient. The expected adverse effects of nitrous oxide/oxygen mixture therapy include nausea, vomiting, dizziness, drowsiness, headache, hypotension, and oxygen desaturation [29]. If any adverse effects occur, the study will be terminated immediately, the patient will be given oxygen, and the adverse effects will be fully reversible in 5 min [43]. Any adverse effects concerning the intervention will be recorded throughout the trial period.

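### Two sections give incompatible instructions after an adverse effect, so gas exposure and the comparability of later pain scores depend on which one staff follow

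*Protocol article*

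**What the plan says.** The Measurement section of the protocol article prescribes: "If any adverse effects occur, the study will be terminated immediately, the patient will be given oxygen". The Interventions section prescribes: "If any adverse effects occur or the patient requests that the trial be discontinued, the data collector can determine whether the trial should continue". It adds that "the project manager will take treatment measures if the patient has adverse effects". The project manager knows which gas is being given; the data collector is described as blind to it.

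The effects that would trigger either rule are listed under Measurement: "The expected adverse effects of nitrous oxide/oxygen mixture therapy include nausea, vomiting, dizziness, drowsiness, headache, hypotension, and oxygen desaturation". No frequency is given for any of them.

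Planned exposure is fixed in Interventions: "the gas intake will last for 15 min". In the comparator arm, "patients in the control group will inhale oxygen by a facemask". Pain and physiological parameters are taken "at baseline (T0), 5 min (T1), and 15 min (T2) after the trial began and at 5 min (T3) after the trial ended".

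**The concern.** Both instructions have the same trigger, the occurrence of any adverse effect, and they lead to different actions. A patient who becomes dizzy or drowsy at minute 6 is taken off the gas and given oxygen under one section. Under the other, that patient may stay on the gas if the data collector so decides. This is a safety instruction that can be read two ways.

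It is also a statistical matter, because the rule followed determines how much study gas a patient receives. The listed effects are those of the nitrous oxide mixture, so early stops should fall mainly, though not only, in that arm. Under the Measurement rule, those patients then breathe the comparator gas. Pain is the primary outcome and is scored at times that fall during or just after inhalation. If stops are concentrated in one arm, the later scores in that arm may be missing, or may be taken under conditions and at times that differ from those of patients who completed the session.

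**Working it through.** **1. The two instructions side by side**

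| | Measurement section | Interventions section |
|---|---|---|
| Trigger | Any adverse effect | Any adverse effect, or a patient's request |
| Action | Stop at once, give oxygen | Continue or stop |
| Who decides | Nobody; automatic | Data collector |
| Who treats | Not named | Project manager |
| Severity threshold | None | None |

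Neither section refers to the other, and neither is said to take precedence. Both use the words study or trial for one patient's session, so the conflict is about that session and not about closing the whole trial.

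**2. Effect on the assessment times**

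Let s be the minute at which inhalation stops, and take T3 as s + 5.

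- Completer: s = 15, so T1 = 5, T2 = 15 and T3 = 15 + 5 = 20 min from gas start.
- Patient stopped at s = 6: T3 = 6 + 5 = 11 min, which is before the scheduled T2 at 15 min.
- In general, T3 precedes T2 whenever s + 5 < 15, that is, for any stop before 10 min.

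T1 is altered only by stops in the first 5 of the 15 min. T2 and T3 are altered by a stop at any time before 15 min. The article does not say whether a stopped patient is still scored at the remaining times.

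**3. The plan's own figure and the time point it belongs to**

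Inputs from Sample size calculation: difference 6.71 − 4.50 = 2.21, SD 1.93, u values 1.96 and 1.282.

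n = 2[(1.96 + 1.282)/(2.21/1.93)]² + 1.96²/4 = 16.03 + 0.96 = 16.99 per group.

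The article prints 16.9 and rounds to 17, so the figure is reproduced. That section takes pain at T1 as its reference. The difference of 2.21 is therefore a T1 figure.

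**4. Illustration only**

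Assume that k of 21 patients in the nitrous oxide arm stop before the score that is analysed, that they have control-level pain, and that 2.21 is the effect in those who complete. The effect in all randomised patients is then 2.21 × (1 − k/21). If the stopped patients' scores are lost and only complete cases are analysed, the estimate stays at 2.21.

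| k | All randomised | Complete cases | Gap |
|---|---|---|---|
| 2 | 2.00 | 2.21 | 0.21 |
| 4 | 1.79 | 2.21 | 0.42 |
| 6 | 1.58 | 2.21 | 0.63 |

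For power (t test, 21 in the control arm, SD held at 1.93), the share stopped in the nitrous oxide arm was varied:

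| Share stopped | Scored, no benefit: difference | Power | Scores dropped: power |
|---|---|---|---|
| 0% | 2.21 | 0.952 | 0.952 |
| 10% | 1.99 | 0.903 | 0.941 |
| 20% | 1.77 | 0.825 | 0.927 |
| 30% | 1.55 | 0.717 | 0.908 |
| 40% | 1.33 | 0.584 | 0.882 |

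None of the values of k or the shares comes from the article. The tables show only that the way stopped patients are handled can matter.

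**The case against.** The textual conflict is hard to dispute. The case on the other side concerns what may be built on it.

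- **Size.** A reader might infer that the trial will overstate its effect by about 24% (0.42/1.79 at k = 4). The article does not support this. The 2.21 belongs to T1, so all four stops would have to occur in the first 5 min. The figure also assumes no benefit at all in those patients, loss of their scores, and a complete-case analysis standing alone. Statistical analysis also names intention-to-treat and replacement of missing values. Nor does the article say whether the pilot, the source of 2.21, already contained stopped patients.
- **Number of stops.** A reader might also infer that the 20% drop-out allowance represents stopping for adverse effects. No cause is given for that allowance, and it is applied to both arms. The Background calls adverse reactions uncommon, and Interventions describes them as mild.
- **Existing provisions.** Pain is scheduled at T1, T2 and T3 with no stated exception for stopped patients. The reason for stopping is already recorded. Staff are trained in managing adverse effects, and a fuller protocol may give the detail on scoring after a stop.

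All of this stands against a quantified bias, and the silence on scoring after a stop is not a fault in itself. None of it removes the contradiction: condensing a protocol can omit a rule, but here two rules are stated and they disagree.

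**Conclusion.** The point holds as a contradiction on the face of the text. It matters first as a safety instruction that staff cannot apply consistently, and second because the rule followed sets exposure and can make T2 and T3 missing or not comparable, with T1 affected only by stops before 5 min. The expectation that this falls mainly on the nitrous oxide arm rests on the listed effects being those of that gas; adverse effects in the oxygen arm come under the same rules.

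The magnitude is unknown and cannot be derived from the article. The gaps of 0.21 to 0.63 points are illustrations under the stated assumptions and should not be cited as an estimate. Confidence is high for the contradiction and low for any particular size of bias. No view is taken on which clinical rule is right.

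**What to change.** 1. The sponsor should reconcile the Interventions and Measurement sections into one rule for what follows an adverse effect, with one named decision-maker. The clinical content is for the sponsor's clinicians.
2. Whichever rule is kept, state that NRS and physiological parameters are recorded at 5, 15 and 20 min from gas start for every randomised patient, including those who stop early. Nothing changes for completers, whose T3 already falls at 20 min.
3. Record the stop time and any gas given afterwards. The reason for stopping is already collected.
4. State that these observed values are used in the intention-to-treat analysis that the article already names.
5. Document which rule was applied to the patients already recruited (20 of 42 at submission).

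The cost is a short clarification and a line on the case form. The patient and data collector are already present, so no visits or staff are added. The limitation is that the change cannot alter data already collected: at submission it could govern at most the remaining 42 − 20 = 22 patients.
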